#### Glenoid Inclination

The glenohumeral joint is also affected by the orientation of the glenoid; thus, the glenoid inclination can aid our understanding of various shoulder conditions. Indeed, an abnormal glenoid inclination might be associated with rotator cuff tears and superior glenohumeral translation [40]. For each participant, the glenoid inclination will be measured on the initial fluoroscopy image as the angle between a line from the upper to the lower glenoid rim (glenoid plane) and a second line set on the floor of the supraspinous fossa [6,40].

#### Greater Tuberosity Angle

The greater tuberosity angle will be measured on the initial fluoroscopy image as the angle between a line parallel to the humerus diaphysis through the glenohumeral joint center and a line from the upper border of the humeral head to the most superolateral edge of the greater tuberosity [41]. A greater tuberosity angle over 70° has been observed to predict rotator cuff tears [41].

#### Subacromial Space

The subacromial space will be measured on the initial fluoroscopic image as the shortest acromiohumeral distance [42,43]. An acromiohumeral distance between 7 mm and 14 mm is usually considered normal, but below 7 mm, has been associated with rotator cuff tears [43]. A narrow subacromial space might compress the supraspinatus tendon, causing pain [44,45].

#### Muscle Cross-sectional Area

Measurements of the muscle cross-sectional area will be performed on the MRI images using dedicated software (Sectra PACS, Sectra Medical Systems). The cross-sectional area of all rotator cuff muscles will be measured at 2 different positions on parasagittal reformatted images [4]. The cross-sectional area of the deltoid will also be measured on the axial plane at the middle of the glenoid [4].

#### Tear Size, Type, and Location

Information about tear size, type, and location will be retrieved from MRI images and previous shoulder reports or previous radiological shoulder images of the patients, if available. Tear size will be classified into (1) partial or (2) complete supraspinatus tendon tear. Tear type will be classified into supraspinatus tendon tear without injury to other rotator cuff tendons (type A) and with injury to other rotator cuff tendons muscles (type B). Both will be used as indicators for injury severity. Additionally, the value of a combined classification will be investigated. Tear location will be defined as the distance from the anterior margin of the tear at the footprint to the intra-articular portion of the bicep. This will allow us to assess whether most anterior fibers of the supraspinatus tendon are intact [46,47]. Tear location will also be analyzed in comparison to shoulder strength and muscle activity. Partial and full-thickness ruptures will be classified according to the classifications of Ellmann [48] and Patte [49], respectively, allowing us to evaluate how advanced the rotator cuff tear is.

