## Methods

### Objectives and Hypotheses

This study will test the overall hypothesis that rotator cuff tears affect glenohumeral translation and that this functional instability depends on the additional load applied, anatomical and morphological variations, and the type and severity of the injury. We propose that greater liMA of the deltoid muscle is associated with greater liTr and that liTr is altered by rotator cuff injury and may be related to patients’ functional scores, muscle cross-sectional area, tear size and type, critical shoulder angle, and glenoid inclination. We also propose that this person-specific relationship is associated with corresponding load-dependent changes in shoulder muscle activity.

Our primary objective is to investigate the dose-response relationship between liMA and liTr in patients with rotator cuff tears and asymptomatic control participants.

Hypothesis 1 is as follows: liMA is positively associated with liTr. Because the shoulder is primarily stabilized by rotator cuff muscles, we expect that the presence of a muscle tear will require additional activity of the remaining intact muscles to stabilize the shoulder. Hence, the dose-response relationship between additional load and relative change in muscle activity with rotator cuff tears will be stronger than in uninjured shoulders.

The secondary objectives are to investigate the in vivo dose-response relationship between additional weight and glenohumeral translation, to understand the biological variation in liTr, the influence of disease pathology on the liTr, the potential compensation by muscle activation and size, and the influence of liTr on patient outcomes. The secondary hypotheses are listed as follows:

Hypothesis 2.1: liTr is greater in shoulders with rotator cuff tears than in healthy shoulders.Hypothesis 2.2: An increase in liTr is part of natural aging, and its variation is related to sex and shoulder anatomy assessed by the critical shoulder angle and the glenoid inclination.Hypothesis 2.3: liTr increases with injury severity and depends on injury type.Hypothesis 2.4: liMA and side-to-side differences in muscle size (ie, muscle cross-sectional area) increase with the presence of injury and injury severity.Hypothesis 2.5: There is a biological variation in liMA and in the compensation effect by muscle activation and muscle size (ie, muscle cross-sectional area).Hypothesis 2.6: Large values of liTr are associated with poor functional scores.

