**Inclusion criteria**
Patients:Aged 45 to 85 years (n=25)Diagnosed unilateral rotator cuff tear: partial or complete supraspinatus muscle tear, with or without injury to other rotator cuff musclesPrior operative treatment of the ipsilateral shoulder or elbowClinical history or symptoms of the contralateral glenohumeral jointRange of motion <30° in abduction and flexionControl participants:Two age groups: 20 to 30 years (n=25) and 45 to 85 years (n=25)No previous known elbow and shoulder injury or symptomsClinical history of the glenohumeral jointPrior conservative or operative treatment of the shoulder or elbowRange of motion <90° in abduction and flexion

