### Experimental Protocol

Each participant will undergo a recruitment and information process before coming to the University Hospital Basel for all planned data collection. Before the assessment, written informed consent will be obtained. Participants will then complete health questionnaires to receive functional scores of the shoulders. Next, fluoroscopic images of a loaded and unloaded 30° shoulder abduction test will be captured, and a 3D motion analysis of the same abduction tests will be performed. Isometric shoulder strength for abduction and internal/external rotation will be assessed with a dynamometer. Finally, magnetic resonance imaging (MRI) images of both shoulders will be taken (Table 1). The estimated total time for each participant is approximately 4 hours. The SPIRIT (Standard Protocol Items: Recommendations for Intervention Trials) checklist, compiled with recommended items to be addressed in a clinical protocol, is provided in Multimedia Appendix 1.

**Table 1 table1:** Schedule of enrollment and assessments.

		Study period	
		Enrollment	Allocation
Time point		Precall	0

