#### MRI Visualization

MRI will be performed using a 3T scanner (Prisma, Siemens Healthineers) with dedicated shoulder and body array coils. No contrast agent will be administered to the participants. Both shoulders will be scanned. The MRI protocol consists of an axial proton density turbo spin echo (TSE) sequence with fat saturation, a sagittal T1-weighted TSE sequence, a sagittal and a coronal T2-weighted BLADE sequence, and a coronal T1-weighted volumetric interpolated breath-hold examination Dixon sequence (Table 2).

**Table 2 table2:** Characteristics of the MRI^a^ sequences.

MRI sequence	Repetition time/echo time (ms)	Slice thickness (mm)	Field of view (mm)	Matrix
PD^b^ TSE^c^ FS^d^ axial	4500/34	2	140	320 × 320
T1 TSE sagittal	762/11	3	159	384 × 384
T2 BLADE sagittal	4210/72	3.6	160	320 × 320
T2 BLADE coronal	3400/75	3.6	150	320 × 320
T1 VIBE^e^ Dixon coronal	4.04/1.23 (TE^f^1) and 2.46 (TE2)	1.3	238 × 332	184 × 256

^a^MRI: magnetic resonance imaging.

^b^PD: proton density.

^c^TSE: turbo spin echo.

^d^FS: fat saturation.

^e^VIBE: volumetric interpolated breath-hold examination.

^f^TE: echo time.

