## Discussion

This experimental protocol will allow for a comprehensive analysis of clinical, functional, and biomechanical data. Furthermore, using MRI, asymptomatic rotator cuff tears will be revealed, aiding our understanding of the effect of rotator cuff tears on glenohumeral motion, especially in asymptomatic shoulders. We expect that rotator cuff tears will have a greater glenohumeral translation and that this will depend on the additional load applied and the anatomical parameters. In addition, a greater liMA of the deltoid muscle is expected with greater liTr. These outcomes might also be associated with muscle cross-sectional area, tear size, and type.

With our infrastructure, electromyographic/motion capture data and fluoroscopy images cannot be acquired simultaneously. Hence, we cannot completely rule out differences in the execution of the abduction tests. However, prior to data collection, exercises will be practiced, and verbal commands will be given to ensure comparable movements.

Glenohumeral translation is an important surrogate for shoulder instability that represents not only functional limitations but also a risk factor for the development of joint degeneration, including osteoarthritis. The results of this study will provide the first evidence of a dose-response relationship between additional weight and glenohumeral translation in patients with rotator cuff tears. Confirming this dose-response relationship and its impact on functional scores and modulating effects by tear type and size, muscle cross-sectional area, critical shoulder angle, and glenoid inclination will elucidate the importance of limiting additional weight during daily activity in this population. Revealing the effects of additional load on muscle activity of the intact rotator cuff tendon in the injured joint will provide evidence of potential overload in these muscles that may lead to secondary damage in other tissues in the injured joint. This study can be considered a proof of concept of a potential diagnostic test (loading shoulder abduction test) for glenohumeral translation. The recommendation based on our results will directly impact activity limitations in patients with rotator cuff tears and influence treatment choice and rehabilitation regimens. The results of this study will be presented at national and international conferences and published in peer-reviewed open-access journals.

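### Tear severity is graded with extra, earlier records named for patients only, so misclassification of severity in Hypotheses 2.3 and 2.4 can depend on symptom status

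*Protocol article*

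**What the plan says.** All references are to the protocol article.

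- **Tear Size, Type, and Location:** the information on these three features is to be "retrieved from MRI images and previous shoulder reports or previous radiological shoulder images of the patients, if available". Size is partial or complete. Type is A or B, according to whether other cuff tendons are injured as well. Of size and type the section says "Both will be used as indicators for injury severity". Tear location is also to be compared with strength and muscle activity.
- **Experimental Protocol** and **MRI Visualization:** at the study visit "magnetic resonance imaging (MRI) images of both shoulders will be taken", and again "Both shoulders will be scanned". One 3T protocol is described, with no distinction by group.
- **Objectives and Hypotheses:** Hypothesis 2.3 is that "liTr increases with injury severity and depends on injury type". Hypothesis 2.4 relates liMA and side-to-side differences in muscle size to both the presence and the severity of injury.
- **Inclusion criteria:** patients enter with a "Diagnosed unilateral rotator cuff tear: partial or complete supraspinatus muscle tear". Controls enter with no known shoulder injury or symptoms.
- **Discussion:** "using MRI, asymptomatic rotator cuff tears will be revealed".

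No earlier source is named for controls. The article does not say which source prevails when the study MRI and an earlier report differ.

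**The concern.** An exposure that is compared across people should be measured in the same way in all of them. Here a common measurement exists, because every shoulder has the study MRI. The stated rule then adds a second source whose availability is tied to having been a symptomatic patient. Two shoulders with the same tendon damage could receive different grades. For example, an injury to a second tendon that is unclear on the study MRI could be settled by an earlier report in a patient, but not in a control.

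Timing adds to this. The schedule puts the functional scores, motion analysis, fluoroscopy, strength testing and MRI at one time point. An earlier report describes the tendon at some other, unstated time. Time since injury is among the characteristics to be summarised, so the interval may well vary between patients.

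At stake is the reading of a severity gradient in liTr or liMA. The Introduction suggests that symptoms may themselves be related to glenohumeral instability. If severity grade partly encodes symptomatic status because of how it was read, part of any gradient, or of its absence, would come from the reading rule rather than from the injury.

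**Working it through.** **1. Sources set side by side.**

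| Shoulders | Study MRI | Earlier reports or images |
|---|---|---|
| 25 symptomatic index shoulders | yes | allowed; likely to exist, since the tear was diagnosed before entry |
| 25 contralateral patient shoulders | yes | allowed; seldom to be expected, since the diagnosed tear is unilateral |
| 50 older-control shoulders | yes | none named; seldom to be expected, given no known injury or symptoms |
| 50 young-control shoulders | yes | none named; seldom to be expected, for the same reason |

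The comments on likely existence are inferences from the eligibility criteria. If the word patients were read loosely to cover every participant, the imbalance would remain, because controls are selected for having no known shoulder problem.

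**2. Number of torn shoulders on each side.** Inputs from Sample Size Calculation: two-thirds of asymptomatic shoulders at age 45 or over are expected to be torn, and 75 torn shoulders are expected in all.

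- Index: 25
- Contralateral: 2/3 × 25 ≈ 16.7
- Older controls: 2/3 × 50 ≈ 33.3
- Total: 25 + 2/3 × 75 = 75, which reproduces the article's figure.

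So 25 torn shoulders are symptomatic and about 50 are not. Severity can be contrasted only within these 75, and the extra records belong mainly to the 25.

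**3. Size of a possible distortion: an illustration, not an estimate.** The documents give no regrading rate, no severity mix and no effect of symptoms on liTr. Assume that:

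- 40% of torn shoulders are truly severe in both groups (10 of 25 and 20 of 50);
- severity has no effect on liTr;
- symptomatic shoulders have 0.8 mm more liTr, a value borrowed from the article's detectable difference;
- earlier records regrade a fraction f of the 25.

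Spurious difference = 0.8 × (symptomatic share of the severe class − symptomatic share of the milder class).

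| Regrading of the 25 | Share, severe | Share, milder | Spurious difference |
|---|---|---|---|
| none | 10/30 = 0.333 | 15/45 = 0.333 | 0 |
| 10% up | 12.5/32.5 = 0.385 | 12.5/42.5 = 0.294 | +0.07 mm |
| 20% up | 15/35 = 0.429 | 10/40 = 0.250 | +0.14 mm |
| 10% down | 7.5/27.5 = 0.273 | 17.5/47.5 = 0.368 | −0.08 mm |
| 20% down | 5/25 = 0.200 | 20/50 = 0.400 | −0.16 mm |

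Against the 0.8 mm that the study aims to detect, these are 9% to 20% in absolute size. They scale with the assumed effect of symptoms and vanish if it is zero. The sign depends on which way the earlier records move the grade, and the article states no rule from which that could be known.

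**4. Effect on stated figures.** Neither the 75 torn shoulders nor any sample size or power statement depends on the source used for grading.

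**The case against.** The strongest case on the other side has four parts.

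*The sentence concerns grading, not whether a tear is present.* This stands. A reader might infer that torn control shoulders would slip into the healthy reference group and distort Hypothesis 2.1, that "liTr is greater in shoulders with rotator cuff tears than in healthy shoulders". The documents do not support that. The index shoulders are torn by the entry criterion, all shoulders share the study MRI as the basis for presence, and contralateral patient shoulders would seldom have earlier records either. Any gap in tear detection between patients and controls would have to come from assumed detection rates.

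*The direction is unknown.* This stands too. It is tempting to say that patient shoulders would be graded up. That requires the more severe reading to prevail, and no such rule is stated. An older report may equally show a smaller tear.

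*The imbalance follows from who is recruited.* This is true as a description of who holds earlier records. It is not a reason to let those records enter the grading, because that is the step that ties the amount of information to symptom status.

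*The article is condensed, and a reading procedure may exist in the full protocol.* This is possible, but the point does not rest on an omission. The article states which sources are used, and for whom. If the full protocol gives the study MRI precedence, the sentence needs only to be brought into line.

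It is also fair to say that grading from the study MRI alone leaves in place any true association between severity and symptoms. It removes only the part that the reading rule would add.

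**Conclusion.** The point holds for severity grading: Hypothesis 2.3, the severity part of Hypothesis 2.4, and the planned comparisons of tear location. Under the stated rule, grading can rest on more information, and on information from another time, mainly in the 25 symptomatic index shoulders, compared with about 50 asymptomatic torn shoulders. It can also be uneven among the patients themselves. Misclassification of severity can therefore depend on symptom status.

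Neither the direction nor the size can be computed from the documents. The 0.07–0.16 mm illustration rests wholly on the assumptions listed with it and could be zero. The conclusion assumes only that earlier records exist more often for diagnosed patients than for people with no known shoulder injury, and that the sentence is applied as written.

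This affects secondary hypotheses and changes no stated sample size or power. It is worth correcting because it is avoidable: a common, contemporaneous source is already planned for every shoulder.

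**What to change.** In Tear Size, Type, and Location, state that the size, type and location used in the analyses are read from the study MRI alone, by the same criteria, in all 150 shoulders. Keep earlier reports and images for describing the patients, or for a sensitivity analysis that repeats the severity analyses with patient grades based on both sources. If that sensitivity analysis is kept, say which source prevails when the two disagree.

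The change is one or two sentences. It needs no new imaging, and no sample size figure changes. The downside is that, in a few patient shoulders, some detail from earlier imaging is not used in the main grading. The sensitivity analysis limits that loss.

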### Statistics and Determination of Sample Size

All study-related data will be entered into and stored using a web-based Research Electronic Data Capture (REDCap; Vanderbilt University) system [50,51]. All statistical analyses will be performed in R statistical software [52]. Overall, 25 patients with 1 symptomatic shoulder with a rotator cuff tear, 25 age- and sex-matched asymptomatic control participants, and 25 sex-matched young control participants will participate in this study. This means that a total of 150 shoulders will enter the analysis. Comparisons between the fluoroscopy-based liTr and motion capture–based liTr will be made. Reproducibility and agreement will be assessed by the mean and standard deviation of differences and Bland-Altman plots. Precision in estimating the liTr will be assessed by average relative standard errors and *R*^2^ values from a global model. Potential deviations from a linear relationship will be assessed by random effects models for a quadratic term. The influence of covariates on the liTr and the biological variation of liTr will be assessed by mixed models applied to the original glenohumeral translation measurements with the liTr as a random effect. Dependence between the shoulders will be considered by bivariate random effects.

#### Participant Characteristics

Descriptive statistics will be used to describe the characteristics of the participants in each group. Mean and standard deviation of age, sex, body height, body mass, BMI, conservative treatment (if applicable), time since injury, and duration of physiotherapy will be calculated to describe the participants.

#### Sample Size Calculation

From a pilot study data consisting of 18 participants (8 patients and 10 asymptomatic controls), we found a correlation of 0.37 between the liTr and liMa for the treatment group and an overall correlation of 0.63 for all individuals included in the study [16]. Using these findings, we considered different correlation scenarios between liTr and liMa for a different power of analysis (Figure 3). For a 5% significance level, 90% power, and a correlation of 0.37, we need 76 shoulders. Considering a possible dropout rate of 5%, we need 80 shoulders for the first hypothesis in this study. We also powered the analysis for the secondary hypotheses and used the repeatability investigation, which suggested a measurement error with a standard deviation of 0.16 mm for the sphere method when assessing the liTr by comparing a load of 3 kg with no load. Moreover, the pilot study revealed a population standard deviation of 1.09 mm for the liTr, suggesting a substantial biological variation in the liTr. Thus, it should be possible to estimate this variation and assess the effect of covariates. Based on our clinical findings, we expect to observe incidental findings of rotator cuff tears in two-thirds of asymptomatic shoulders in participants aged 45 years or older. Therefore, we expect to have 75 shoulders with rotator cuff tears. Within the 75 shoulders with rotator cuff tears, it will be possible to detect a difference of 0.8 mm in liTr with a power of 90%.

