In this study, the correlation between liMA and liTr and their relation to patients’ functional scores, muscle activation and size, tear size and type, and shoulder anatomy (critical shoulder angle and glenoid inclination) will be analyzed.

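### Hypothesis 1 is sized as a liMA–liTr correlation that needs several groups combined, but no group or tear term is named, so group differences could be read as association

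*Protocol article*

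**What the plan says.** All references are to the protocol article.

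- **Objectives and Hypotheses.** The primary objective covers patients and asymptomatic controls together. Hypothesis 1 (H1) reads "liMA is positively associated with liTr", with no condition on group. The section closes by naming what will be analysed, and it names a correlation: "the correlation between liMA and liTr and their relation to patients". Hypothesis 2.1 expects higher liTr in torn shoulders, and Hypothesis 2.4 expects liMA to increase with injury and its severity.
- **Sample Size Calculation.** The pilot had 8 patients and 10 controls. Among the patients liTr and liMA correlated at 0.37; with both groups together the article gives "an overall correlation of 0.63 for all individuals included in the study". The design step is "For a 5% significance level, 90% power, and a correlation of 0.37, we need 76 shoulders". Allowing for 5% dropout raises this to 80 for H1. The section expects 75 torn shoulders.
- **Statistics and Determination of Sample Size.** Three groups of 25 participants are planned: "This means that a total of 150 shoulders will enter the analysis". Mixed models are planned for covariate effects on liTr, with bivariate random effects for the two shoulders of one person. This text mentions neither liMA, nor H1, nor a group or tear term.

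**The concern.** H1 is a mechanistic claim: within comparable shoulders, more deltoid activation goes with more translation. If tears raise both measures, as the protocol itself predicts, the two will be correlated across a mixed sample even when they are unrelated inside every group. A significant overall correlation could then mean only that torn and untorn shoulders differ on both measures, which is already the subject of Hypotheses 2.1 and 2.4.

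The planning value and the sample do not match either. The 0.37 was observed within patients, but the number of shoulders derived from it can be reached only across groups. The protocol does not say whether H1 targets the within-group relation (pilot 0.37 in patients) or the overall one (pilot 0.63).

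**Working it through.** **1. The plan's own figure.** Inputs: r = 0.37, alpha 5% (two-sided assumed; the article does not say), power 90%.

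- Fisher z: ((1.960 + 1.282)/atanh(0.37))² + 3 = 72.6, so 73 shoulders. The bias-corrected version gives 72.
- Untransformed: (1.960 + 1.282)²/0.37² = 76.75, close to the stated 76.
- Power at 76 is 91.3% to 91.6%, so the stated number is slightly conservative.
- Dropout: 76/0.95 = 80, which reproduces.

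The number itself is not the problem.

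**2. Is combining groups implied?** One group supplies 25 × 2 = 50 shoulders. Expected torn shoulders are 75. Both fall short of 80. At r = 0.37 the power is 46% in the 25 symptomatic shoulders, 77% in 50 shoulders, 91% in 75 and 99.7% in 150 (shoulders independent). So the sample size for H1 can be met only by combining groups.

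**3. What combining does without adjustment.** Let r_w be the within-group correlation, d1 and d2 the group shifts in SD units, p the share of shoulders shifted, and q = p(1 − p). Then

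pooled r = (r_w + q·d1·d2) / √[(1 + q·d1²)(1 + q·d2²)].

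Take r_w = 0 and 75 torn and 75 untorn shoulders, so q = 0.25. The article gives the direction of the shifts but not their size, so a range is assumed. The value 0.73 SD is the article's detectable liTr difference over its SD, 0.8/1.09. It serves only as a scale, and any matching shift in liMA is an assumption. Rates are for a 5% two-sided test with shoulders treated as independent. Simulation (4,000 runs per row) agreed with the formula.

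| Shift in liTr / liMA (SD) | Pooled r | Significant, N = 80 | Significant, N = 150 |
|---|---|---|---|
| 0.25 / 0.25 | 0.015 | 5% | 5% |
| 0.5 / 0.5 | 0.06 | 8% | 11% |
| 0.73 / 0.5 | 0.08 | 11% | 17% |
| 0.73 / 0.73 | 0.12 | 18–19% | 31% |
| 1 / 1 | 0.20 | 43–46% | 70% |

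Example for the last row: 0.25/(1 + 0.25) = 0.20.

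With a torn/untorn term, the simulated rate was 4.5% to 5.4% in every row and at both sample sizes. That holds when the adjusting factor is the one that carries the shift.

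**4. Sensitivity to who carries the shift.** For 1 SD in both variables and N = 150:

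- One third of shoulders shifted: q = 2/9, r = 0.222/1.222 = 0.18, about 61% significant.
- Only the 25 symptomatic shoulders shifted: q = (1/6)(5/6) = 0.139, r = 0.139/1.139 = 0.12, about 32%.

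**5. What the pilot can show.** With 8 and 10 participants, q = 80/324 = 0.247. If r were 0.37 in both groups, a pooled 0.63 needs q·d² = (0.63 − 0.37)/(1 − 0.63) = 0.703, so d = √(0.703/0.247) = 1.69 SD in both variables. If r were 0 in both groups, q·d² = 0.63/0.37 = 1.703 and d = 2.63 SD. The correlation within controls is not reported, and a higher value there would also produce 0.63. Approximate 95% intervals, counting participants, are −0.45 to 0.85 for 0.37 (n = 8) and 0.23 to 0.85 for 0.63 (n = 18).

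**The case against.** The strongest reply is that the article never says H1 will be tested by an unadjusted pooled correlation. H1 speaks of association, mixed models with covariates are planned for liTr, and the list of fixed effects is commonly left to an analysis plan, which is not shown. The count of 150 shoulders does not exclude a group term. The sample size also uses the smaller, within-patient 0.37 rather than 0.63, and H1's rationale itself contrasts torn with uninjured shoulders. Finally, the primary objective covers patients and controls together, so an overall association is a legitimate quantity to report.

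Much of this stands. A reader might infer that an unadjusted pooled test is the plan, or that the rise from 0.37 to 0.63 shows mixing at work. The documents support neither. A reader might also suspect that several loads per shoulder will be pooled as separate points. liMA is computed per load, but the sample size counts shoulders and nothing says loads will be pooled, so that is conjecture.

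What does not stand is that this is only omitted detail. The target of the primary hypothesis belongs in the protocol, and here a within-patient planning value is paired with a sample that must span groups. The mixed-model text does not mention liMA. The bivariate random effects deal with two shoulders of one person, not with mean differences between groups. H1's contrast of torn and uninjured shoulders concerns load and activity, not liMA and liTr.

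**Conclusion.** The point holds in a conditional form. H1 is framed and sized as a correlation that needs groups combined, the protocol predicts injury shifts in both variables, and no group or tear term is named for it. If the correlation is taken unadjusted, H1 can be confirmed with no within-group association.

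The size depends on shifts that the article does not give: no inflation at 0.25 SD, modest at 0.5 SD (11%), and serious at 0.73 to 1 SD (31% to 70%), for 150 shoulders split evenly by tear status and treated as independent. If fewer shoulders carry the shift, the rates are lower. More extreme figures, such as a separation of 1.7 SD, require the control correlation to equal that of patients and should not be taken as an estimate. The pilot values are compatible with mixing but do not demonstrate it.

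**What to change.** State in the protocol that H1 is tested on the within-group association: a mixed model of fluoroscopic liTr on deltoid liMA, with a fixed effect for recruitment group or MRI tear status and a participant random effect. Add a load term if several loads per shoulder are analysed. Choose between recruitment group and tear status in advance, since adjusting for one need not remove a shift carried by the other. MRI of both shoulders is already scheduled, so tear status will be available. Report the unadjusted overall correlation alongside as secondary.

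The cost is a sentence of analysis text, two or three degrees of freedom, and a probably smaller reported association. For a within-group r of 0.37, the requirement is about 75 shoulders (73 plus one or two for the group terms). Power with 150 shoulders stays at about 99.7%, again treating shoulders as independent.
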